# Rehabilitation of Executive function in Paediatric Traumatic brain injury (REPeaT): protocol for a randomized controlled trial for treating working memory and decision-making

**DOI:** 10.1186/s12887-018-1338-x

**Published:** 2018-11-20

**Keywords:** Traumatic brain injury, Paediatric, Working memory, Decision-making, Executive function, Cogmed, Computerized cognitive training, Intervention, Randomized controlled trial (RCT), Functional outcomes

## Abstract

**Background:**

Working memory allows us to hold information in an active state for short periods of time, and is essential in facilitating goal directed cognitive functioning. Difficulties in working memory and decision-making are common post childhood Traumatic Brain Injury (TBI). Despite this, there is a paucity of research pertaining to implementation and effectiveness of interventions to reduce these common difficulties which impact significantly on one’s ability to function independently. One such intervention, Cogmed Working Memory Training Program, has shown success in improving working memory in other childhood clinical populations, but has received little evaluation in the TBI area. This study aims to evaluate whether Cogmed improves working memory and decision-making post childhood TBI and whether these benefits generalize to functional areas.

**Methods:**

The study is a randomized controlled trial (RCT) of the Cogmed (RM version) intervention for children post-TBI. Children aged 7–15 years are initially screened for working memory impairments. Eligible participants are then randomized into either the treatment group (Cogmed) or the active-control group (Lexia Reading). Each group trains online for 50 min each day, 5 days per week, for 5 consecutive weeks. The online training is supported by online clinician meetings each week. Outcome neuropsychological and functional assessments are carried out immediately at the completion of the intervention and at 6 months follow-up.

**Discussion:**

This study follows gold standard methodology in intervention research; uses a novel measure of decision-making; measures the effects of intervention on functional outcomes immediately and longer-term post intervention; uses online clinician support in order to allow more families easy access to the program; and promotes the use of technology to improve health services. If efficacious in improving working memory, decision-making, and functional outcomes, our team will then take a key role in implementing Cogmed into clinical care.

**Trial registration:**

Australian New Zealand Clinical Trials Registry ACTRN12617000085370. Trial Registration Date: 16/01/2017. Protocol Version/Date: HREC 35181G/18.08.2017. Study Status: Ongoing.

## Background

Paediatric Traumatic Brain Injury (TBI) is one of the leading causes of death and disability in children and adolescents worldwide. TBI is defined as “an alteration in brain function, or other evidence of brain pathology, caused by an external force to the head” [1]. Substantial literature on paediatric TBI has identified acute and long-term impairments in higher order cognitive processes often identified as impairments in executive function (EF) [2–4].

Definitions of EF indicate that it encompasses the highest level of human functioning such as working memory (WM), decision-making (DM), aspects of attention, cognitive control, and inhibition [5, 6]. Neural substrates linked to WM and DM include the frontal lobes, prefrontal subregions, posterior cortex, and subcortical structures [7–9] These brain regions mature from childhood into early adulthood with different trajectories across sex and are specifically vulnerable following TBI sustained in childhood [10–12]. Findings from brain imaging studies also suggest that the integrity of these brain regions and the neural circulatory connecting them is crucial for WM [13, 14] and DM [6, 15–17]. With regards to sex, previous research shows difference in performance on WM and DM tasks in girls and boys post childhood TBI [12, 18].

WM is a limited multi-component system that facilitates maintenance and manipulation of information in an active state for short period of times. It is involved in goal-directed cognitive functioning and in the acquisition of academic skills including mathematical computation, reading, and writing [19–24]. Impairments in WM post TBI are common, often with implications in a multitude of cognitive processes and adaptability in daily life [25, 26].

DM is defined as the fundamental skill for identifying, processing, and selecting one course of action from multiple alternatives [27]. Thus, DM is a stepwise process as proposed by the process tracing models of DM [28]. Myriad disciplines have studied DM from different theoretical assumptions ranging from normative theories of subjective expected utility [29], to dual process theories of information processing [30, 31], and to somatic marker hypothesis [32], with less research on process tracing methods of information acquisition in DM [33]. One such method pertains to the use of information boards [34–36]. More recently, an emerging field of decision neuroscience has led to an integrated study of DM by taking into account the neural substrates, cognitive processes, and the association between one’s decisions and social outcomes [4, 37–39]. Findings from these studies suggest WM allows multiple units of information to be assimilated and compared in DM [4, 40]. Additionally, DM has also been associated with functional outcomes such as return to school. In TBI, recent studies have also indicated deficits in DM [41–47]. While there are studies that contradict DM’s association with WM in children with or without brain injuries, findings in support of this association demonstrate a pleading case for more research in this area [48–54].

It is clear that EF domains such as WM and DM provide a target for intervention, given they are frequently impaired post childhood TBI, and are associated with everyday function and social functioning. Previous studies estimate that one-third of children post TBI benefit from intervention approaches [55]. Recently, several computerized interventions or training programs have been successfully trialled for executive function rehabilitation in other clinical populations. Despite this, there is a paucity of research in the intervention area, with even less research pertaining to the effectiveness of interventions implemented following childhood TBI [56, 57]. Methodological limitations of existing research include reliance on case studies instead of RCT design; no preregistration of trials; lack of an active-control group, no blinding, small sample size, and limited use of clinically meaningful outcome measures [58].

The Cogmed Working Memory Training program (Cogmed), is a popular computerized cognitive intervention that is based on the multi-component theory of memory [59] and the theory of neuroplasticity [26]. Cogmed was first trialled in an RCT of 53 children with ADHD [60]. This trial aimed to investigate the impact of Cogmed in improving WM in this clinical population. Results immediately post-intervention and at 3 months follow-up suggested significant benefits in working memory, ADHD symptoms, and several other executive tasks thereby implying the benefits from the intervention were also transferrable. Since then Cogmed has been trialled in typical adults [61], pre-term children [62], children with ADHD, and school-aged children with low WM [63, 64]. However, evidence for benefits from Cogmed in children with TBI is scarce, where to date only seven published studies have investigated the efficiency of Cogmed post brain injury. Of these, six studies involved adults with acquired brain injuries [65–70]. Additionally, limitations of these studies included small sample size, lack of an active-control group, and shorter length of follow-up. A single recent study involving children post-TBI [57] investigated the impact of Cogmed on various components of WM. Findings from this study provided preliminary evidence for the efficacy of Cogmed in improving WM, attention, and academic skills. However, findings are limited by a small sample size, lack of consideration of injury-related factors, and short length of follow-up post intervention. While research investigating the impact of Cogmed in brain injuries supports improvements in similar tasks as those in Cogmed training, other results are inconclusive. [71]. Hence, further research investigating the efficacy of Cogmed in improving performance in similar tasks as well as generalizability to other functional outcomes is required.

In summary, ours is the first study to use a novel task of DM to investigate the relationship between WM and DM, and to study the impact of Cogmed on WM, DM, and functional outcomes in paediatric TBI.

## Study aims

The overall aim of the proposed study is to evaluate the effectiveness of Cogmed post childhood TBI. RCT methodology with the inclusion of an active-control group and a larger sample size will be implemented to address previous limitations in this area. In addition to the primary executive function outcomes post intervention, this trial will investigate the generalized impact (far transfer) of Cogmed in improving everyday function including social functioning. The follow-up assessments will be completed at two time points, namely, immediately post-intervention, and at 6-months follow-up. This RCT will be a novel study to identify the relationship between WM, DM, functional outcomes and the impact of Cogmed in all these areas in children post TBI.

It is hypothesized that: (a) immediately post-intervention and at 6 months post-intervention compared to the active-control group the treatment group will report improvements in WM and DM; (b) improvements in WM will be associated with an increase in DM, academic achievement (mathematics), social skills, behavioural, and quality of life outcomes; and (c) age and sex will have an impact on WM and DM of children post- TBI (see Fig. 1).

**Fig. 1 Fig1:**
[figure not shown]
The proposed model of this study

## Methods/design

### Approval and registration

This study has been approved by the Human Research Ethics Committee of the Royal Children’s Hospital, Melbourne (HREC 35181), and prospectively registered with the Australian New Zealand Clinical Trials Registry (ACTRN12617000085370).

### Design

This study follows the gold standard methodology of intervention research. Conducted and reported according to CONSORT guidelines, it is a double-blinded, active-controlled, randomized trial. Data from neuropsychological assessments of participants, and parent and teacher questionnaires will be collected at four different time-points (see Fig. 2): T0 Study eligibility is determined by screening for working memory impairments in the child at least post 6 months after TBI; T1 Following inclusion of an eligible participant, pre-intervention baseline assessment conducted and data collected; T2 Immediately post-intervention assessment; T3 6-month follow-up post intervention assessment. At all four time points, data will be collected from both the treatment group and the active-control group.

**Fig. 2 Fig2:**
[figure not shown]
Study design

### Setting

This study will be conducted at the Murdoch Children’s Research Institute (MCRI) and The Royal Children’s Hospital (RCH), Australia. Participants will be recruited from The RCH Victorian Paediatric Rehabilitation Service (VPRS) state-wide registry, audit of presentations to The RCH, or from previous research projects conducted at The RCH. The study is expected to run for a 24 month period, with participant identification and recruitment, randomisation, and intervention implementation carried out over 18 months, followed by the 6 month follow-up post-intervention for all the study participants.

### Participants

Children who have had a TBI will be contacted to participate in the study via their parent/guardian. To be eligible to participate in the RCT, children will be required to meet the following inclusion criteria: (1) sustained a TBI where there was head trauma associated with a) altered consciousness, as defined by Glasgow Coma Score between 3 and 15 and/or post traumatic amnesia, or b) intra-cranial traumatic abnormalities on brain scan; (2) evidence of reduced working memory or executive dysfunction at screening (see Table 1); (3) attend primary or secondary school and be between the ages of 7–15 at the time of the intervention; and (4) a minimum of 6 months post-TBI.

**Table 1 Tab1:** Summarises the study measures and data collection time-points

Outcome	Measure	Respondent	Criteria for inclusion	Time point			
				T0	T1	T2	T3
Screening outcome							
Intellectual functioning	Wechsler Abbreviated Scale of Intelligence-Second Edition (WASI-II) [76]	Child	FSIQ> 70	X			
Working memory	AWMA-Screener [75]	Child	Score on any one of the sub-test < 1 SD below the mean	X			
Executive function	Behavioral Rating Inventory of Executive Function (BRIEF) [77]	Parent	Score on any one of the sub-test < 1 SD below the mean	X			
Primary outcome							
Working memory	AWMA-S [75]	Child			X	X	X
Decision-making	The Decision-Making Task [34]	Child			X	X	X
Secondary outcome							
Working memory	Wechsler Intelligence Scale for Children-Fifth Edition (WISC-V): Digit Span [78]	Child			X	X	X
Decision-making	The Jumping to Conclusions: the Beads Task [79]	Child			X	X	X
Academic achievement (Mathematics)	The Wide Range Achievement Test: Fourth Edition (WRAT-IV): The Math Computation [80]	Child			X	X	X
Adaptive behaviour	Behavioral Rating Inventory of Executive Function (BRIEF): Global Executive Composite [77]	Parent (BRIEF-P) Teacher (BRIEF-T)			X	X	X
	Child Behaviour Checklist (CBCL) & Teacher Report Form (TRF) [81]	Parent (CBCL) Teacher (TRF)			X	X	X
Social skills	Social Skills Improvement System Rating Scales (SSIS) [82]	Parent(SSIS-P) Teacher(SSIS-T)			X	X	X
Quality of life	Paediatric Quality of Life (PedsQL) [83]	Parent			X	X	X

T0: Screening; T1: Pre-intervention baseline assessment; T2: Immediately post-intervention assessment; T3: 6 months follow-up post intervention assessment

Ineligibility for participation in the study will be determined by the following exclusion criteria: (1) non-fluency in English; (2) IQ below 70 at screening (3) other previously documented neurological or learning difficulties diagnosis; (4) severe sensory or physical impairment that affects their capacity to attend mainstream school and complete the training program; (5) families and/or primary caregivers who are unable to support/assist their child through to the completion of the intervention program. This will be determined through discussions with primary caregivers/parents during the recruitment phase.

### Recruitment and allocation

Recruitment will begin with the identification of children who meet the inclusion criteria for a diagnosis of TBI and their current age. Parents/guardians of children will be approached through the tracing letter. After 2 weeks, the research team member will follow-up with a phone-call to provide them with more information about the study. At this time, if the parent/guardian declines their consent for participating in the study, they will be excluded.

When a parent/guardian indicates interest in their child’s participation a letter of invitation to the study will be sent, along with the detailed study information statement and consent form. After the informed written consent is obtained, the first appointment for child’s screening assessment will be arranged at the family’s convenient time. This appointment (T0) will include cognitive screening for working memory impairments and IQ, and if eligible, (T1) the pre-intervention neuropsychological baseline assessment. Eligible participants then will be randomly allocated either to the treatment group or the active-control group.

Parent/guardians will also be provided with the teacher questionnaires along with a reply-paid envelope to forward to their child’s teacher for completion. Teacher consent to participate will be implied in the completion of questionnaires.

### Randomization

Following the first study appointment, eligible participants will be randomized in a ratio of 1:1 to the treatment group or the active-control group. The randomization list will be generated using online software (sealed envelope™) by an independent statistician. Block randomization will be used to generate treatment allocations. At the time of randomization, participants will be allocated the next available sequential study number in an opaque sealed envelope. Allocation of participants to the relevant study group is managed by the chief investigator and will remain blind to the participant, their family and all other members of the trial team. The participants will be also blinded as to which program they have been assigned. However once the program is commenced treatment allocation may become clear to participating families.

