### Intervention delivery

Participants in the treatment group will be administered Cogmed ™ (RM version) program. Developed for children aged 7 years and above, it is a commercially available [72] online adaptive working memory training program. For the purpose of this study, participants will train on the standard protocol consisting of a total 25 training blocks to be completed over a span of 5 weeks. Participants will be required to complete one training block in 50 min every day for 5 days a week for 5 weeks. Each training block includes a series of interactive and adaptive exercises that not only targets but also dynamically adapt to the visuo-spatial and verbal WM ability of the participants at the time of the training. During the training, if the participant makes consecutive errors on four trials, the program will automatically enforce a mandatory break for 15 s. At the completion of each training block, the participant gets rewarded with a reward game, RoboRacing.

Cogmed training will be completed online by the participants from their homes. It will be supervised by a trained Cogmed Coach who is the study co-ordinator. Once the participants are randomized to the treatment group, the Cogmed Coach will conduct a Start-up session with the participants and their Training Aides. In this session, the Cogmed Coach will (a) provide an information sheet to set up the program on the home computer or iPad, (b) explain the training structure, (c) plan the training times (d) discuss participants’ motivation and expectations, (e) discuss reward system, (f) schedule online weekly meetings, and (g) fill out the Cogmed Questionnaire. Online meetings (through Skype Business/Google Hangouts/GoTo Meetings) will be held once per week for 5 weeks of training to provide support and answer any queries.

The training performance and compliance will be monitored through a secure server by the Coach.

The program requires internet access and if necessary families will be provided with an internet-connected iPad for the duration of the program. The coach can monitor the training and compliance by logging into a secure server. Program compliance can be assessed as the number of sessions completed by each child, and time spent per session will be recorded.

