### Implementation of active control*:* Lexia Reading Core5

Participants in the active-control group will be administered commercially available Lexia Reading Core5 [73, 74]. An adaptive computerized reading program, Lexia battery caters for all age groups of children but has no memory training component. Consisting of a total 18 level and 89 activities, it delivers structured, in-depth, and individualized training in six areas of reading – Phonological Awareness, Structural Analysis, Vocabulary, Phonics, Fluency, and Comprehension. Each participant will first complete 20 min of auto-placement on their initial log-in to Lexia Reading Core5. Auto-placement is a tool that assesses participant’s current level of functioning. Based on this performance, participants will be assigned an appropriate program level for their training. Once participants successfully complete a prescribed set of units, they will progress to higher levels of the program. In addition to the online training, Lexia also provides supplementing individualized paper-based practice materials for participants struggling on a particular activity. On successful completion of a level, the participant is rewarded with a certificate. Participants will train on Lexia Reading Core5 for 50 min each day for 5 days a week for 5 weeks at their homes.

The Lexia program provides an active- control for the experience of sitting in front of a computer and engaging with fun learning tasks randomized to the participants in the active-control group. As with Cogmed, the coach will provide assistance with the set-up and weekly online meetings.

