### Data storage

Data will be collected in both pen-paper and digital format and securely stored at MCRI. Only this study’s chief investigators will have access to the collected data, both throughout and after the conclusion of the study.

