### Strengths and limitations

This study has notable strengths. The trial will follow the gold-standard methodology in intervention research, i.e., double-blind, randomized-controlled, pre-registered with clinical trials registry, inclusion of active-control group, large sample size, and long duration of follow-up. There is limited research on DM, the relationship between WM and DM, and the efficacy of Cogmed in a paediatric TBI population. This study will address these gaps in the literature. DM deficits are typically assessed using tasks that are limited in their ability to replicate everyday functioning. A novel measure of DM has been developed in order to measure naturalistic decision-making processes in children. To our knowledge, this is the first trial investigating the impact of Cogmed on WM, DM, and functional outcomes in TBI population. The use of online training programs and online clinician support will ensure fewer burdens on families, higher participation, and adherence to training.

Predicted challenges of this study include recruitment of such a large sample size with respect to a screening component, ensuring participant adherence to training regardless of randomisation, and participant follow-up**.** Another limitation pertains to the blinding of participating families. While the research personnel responsible for screening participants and administering outcome assessments are completely blinded, it is not possible to completely blind the parents to the training programs.

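### The trial is labelled double-blind, but the co-ordinator who coaches both arms must know allocation and families cannot be reliably blinded, so the parent-rated secondary outcomes are unblinded

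*Protocol article*

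**What the plan says.** All references are to the protocol article.

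- **Label.** The Design section states that "it is a double-blinded, active-controlled, randomized trial". Strengths and limitations repeats the label as a strength: "double-blind, randomized-controlled, pre-registered with clinical trials registry".
- **Who is blind.** Under Randomization, "Allocation of participants to the relevant study group is managed by the chief investigator", and allocation "will remain blind to the participant, their family and all other members of the trial team". The same paragraph then allows that families may work out their allocation once training starts.
- **Who delivers training.** Intervention delivery says of the Cogmed training: "It will be supervised by a trained Cogmed Coach who is the study co-ordinator". The coach runs the start-up session after randomization, meets the family online each week and follows training on a server. For the control arm, the section on Lexia Reading Core5 says: "As with Cogmed, the coach will provide assistance with the set-up and weekly online meetings".
- **Parents and assessors.** Strengths and limitations concedes that "it is not possible to completely blind the parents to the training programs". The same sentence says that the staff who screen children and give the outcome assessments are fully blind.
- **Raters.** Table 1 gives BRIEF, CBCL/TRF and SSIS a parent form and a teacher form each. PedsQL has a parent form only. AWMA-S, the Decision-Making Task, Digit Span, the Beads Task and WRAT-IV Math Computation are completed by the child.

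**The concern.** The article claims a property that its own delivery arrangements rule out. The co-ordinator belongs to the trial team and must know who trains on which program, yet the Randomization sentence exempts only the chief investigator. The stated limitation covers parents and says nothing of the coach.

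This matters because transfer to everyday and social function is a declared aim, and hypothesis (b) under Study aims names social, behavioural and quality-of-life outcomes. Parents contribute ratings on most of those measures. If parents in the two arms expect different benefits, their ratings can differ with no true change in the child. Under a double-blind label, a reader would take such a difference as blinded evidence.

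**Working it through.** The blinding question is settled by comparing sections. The arithmetic only illustrates what rater bias could do.

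**1. Can the Randomization sentence be true?**
- Randomization: everyone except the chief investigator is blind.
- Intervention delivery: the co-ordinator coaches each Cogmed child.
- Lexia section: the coach also sets up and meets the Lexia families. The only coach identified is the co-ordinator.
- Facilitator training and program fidelity: the co-ordinator was trained in both programs.

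The co-ordinator therefore knows the arm of every child. Even if someone else coached Lexia, knowing which randomized children are on Cogmed would reveal the rest, since there are only two arms. The sentence is false for the co-ordinator, and the article's own caveats make it unreliable for families.

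**2. Which outcomes are exposed? (Table 1)**

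| Functional measure | Parent | Teacher | Child test |
|---|---|---|---|
| Mathematics (WRAT-IV) | – | – | yes |
| BRIEF | yes | yes | – |
| CBCL / TRF | yes | yes | – |
| SSIS | yes | yes | – |
| PedsQL | yes | – | – |

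- Parents rate 4 of the 5 functional measures; 3 of those 4 also have a teacher form.
- Counting score sources: 4 parent + 3 teacher + 1 child test = 8, so parents supply 4/8 = 50%.
- Adding Digit Span and the Beads Task gives 10 secondary score sources, 4 of them from parents.
- Both primary outcomes are child-completed and do not depend on parent ratings.
- Teacher forms are better protected but not certainly blind: under Recruitment and allocation they reach the teacher through the parent, and teacher blinding is not stated.

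**3. What could a rating bias do? (illustration)**

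Inputs: 37 per arm (Participant flow and estimated sample size) and a 0.05 significance level (same section; two-sided assumed). Assumptions: no true effect, all 74 children rated, and a between-arm rating bias of *b* SD. The protocol gives no value for *b*.

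The two-sample t statistic is then noncentral t with 2 × 37 − 2 = 72 degrees of freedom and noncentrality *b* × √(37/2) = 4.30 × *b*. The false-positive rate is the probability that it falls beyond the two-sided 5% critical values.

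| Assumed *b* (SD) | Noncentrality | False-positive rate |
|---|---|---|
| 0 | 0 | 5.0% |
| 0.1 | 0.43 | 7.1% |
| 0.2 | 0.86 | 13.6% |
| 0.3 | 1.29 | 24.7% |
| 0.5 | 2.15 | 56.4% |

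These rates are per scale. Only a difference in bias between arms counts; a shift common to both arms cancels.

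**The case against.** The strongest reply is that the article already discloses the weak point and protects the outcomes that matter most. Incomplete family blinding is admitted under both Randomization and Strengths and limitations. Outcome assessors are stated to be fully blind. The comparator is well matched: also adaptive and commercial, with the same 50 minutes, 5 days and 5 weeks, coach set-up, weekly meetings and rewards. That matching should reduce any difference in expectation. All of this stands, and it confines the point to the parent-rated secondary outcomes. It does not rescue the label or the Randomization sentence, because the coach's knowledge of allocation is nowhere acknowledged.

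A reader might infer more than the document supports in four ways:

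- **That the far-transfer claims as a whole rest on unblinded ratings.** They do not: three of the four parent-rated measures have teacher forms, and mathematics is a test.
- **That the co-ordinator could sway testing or scoring.** No section gives the co-ordinator a role in outcome assessment, and the statement on assessors implies there is none.
- **That allocation and data sit in the same hands.** Data storage says that only the study's "chief investigators will have access to the collected data", but that is a storage rule. Masking of the analyst is a matter for the full protocol or SAP, and its absence from an article is no fault.
- **That parents certainly know and favour their program.** The article says only that allocation may become clear and that blinding cannot be complete. A between-arm difference in expectation is plausible but not established.

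**Conclusion.** The point holds in limited form. The double-blind label and the Randomization sentence conflict with the delivery arrangements and with the article's own concessions, and they need correcting. This part rests on the text alone.

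The consequence is confined to BRIEF-P, CBCL, SSIS-P and PedsQL. It is sharpest for PedsQL, where quality of life has no second rater. The primary comparisons and mathematics are not called into question by this point, given that the statement on blinded assessors holds.

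The size of any bias is unknown. The range of about 7% to 56% depends wholly on the assumed 0.1 to 0.5 SD between-arm bias and is not an estimate for this trial.

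**What to change.** 1. In Design and in Strengths and limitations, replace double-blind with: outcome-assessor-blinded; coach/co-ordinator unblinded; families not reliably blinded.
2. Correct the Randomization sentence so that it agrees with Intervention delivery and the Lexia section, naming the co-ordinator among those who know allocation.
3. State that the coach/co-ordinator and the chief investigator who manages allocation take no part in testing or scoring at the post-intervention (T2) and 6-month (T3) assessments. The statement on blinded assessors already implies this.
4. Report parent-rated results, PedsQL above all, as unblinded and open to expectation bias. A parent-rated difference on its own should not be presented as blinded evidence of functional transfer. Teacher forms and mathematics are the better-protected evidence, with a note that teacher blinding is not stated.

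The cost is a change of wording and a role rule for existing staff, with no new data and no change in sample size. The downside is a weaker blinding claim in the final report.
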